# FIRE Stones: impact of forced diuresis on the residual fragment rate after flexible ureteroscopy for destruction of kidney stones with laser—protocol for a randomized controlled two-parallel group multicenter trial with blinding evaluation

**DOI:** 10.1186/s13063-024-08309-0

**Published:** 2024-07-04

**Keywords:** Kidney stones, Flexible ureteroscopy, Forced diuresis, Furosemide, Stone-free rate, Residual fragments, Lithiasis patient, Randomized trial

## Abstract

**Background:**

Lithiasis is a common and recurrent disease. Flexible ureteroscopy (fURS) is the cornerstone of laser treatment of kidney stones. Kidney stones destruction requires its laser pulverization into small fragments in order to remove them through the ureter or improve their spontaneous expulsion along the urinary tract. However, most of the time, all the micro-fragments and dust created cannot be extracted using our surgical tools and may stay intra-renally at the end of the procedure. Adjuvant treatments (such as forced diuresis, inversion or mechanical pressure) were previously described to improve the expulsion of stone fragments after extra-corporeal shock wave lithotripsy. Nevertheless, the impact of adjuvant treatment after fURS remains unclear and mainly theoretical.

**Objective:**

The primary objective is to show that the injection of 40 mg of furosemide in slow intravenous during 10 min, after the procedure, increases the stone-free rate 3 months after a fURS for destruction of kidney stones with laser.

**Methods/design:**

The study will be a two-parallel group randomized, controlled, multicentric trial with a blinding evaluation. Nine French departments of urology will participate. Patients will be randomized in 2 groups: the experimental group (injection of 40 mg of furosemide at the end of the surgery) and a control one (usual care). Patients will be followed up for 3 months (± 2 weeks) after the surgery. Then, we will perform a low dose abdomino-pelvic CT scan. The primary outcome is the stone-free rate at 3 months. A centralized review of the images will be performed by two specialized radiologists, in a blind and crossed way to allow a homogenization of the results. The secondary outcomes will include the rate of early post-operative urinary tract infection (UTI), the evaluation of post-operative pain, and the safety of the use of furosemide in patients treated by fURS for renal stone laser destruction. As secondary objectives, it is also planned to look at the effect of the prescription of an alpha-blocker as usual treatment on stone-free rate and to assess the agreement between the imaging analysis of the urologist and the specialized radiologist.

**Discussion:**

Lithiasis is a public health problem. It affects about 10% of the general population. This prevalence is increasing (multiplied by 3 in 40 years), partly due to changes in the population’s eating habits over the years. The lithiasis patient is a patient with a chronic disease requiring annual follow-up and who may suffer from multiple recurrences, with a recurrence rate at 5 years of 50%.

Recurrences are partly due to residual fragments left in the kidneys at the end of the operation. Other risk factors for recurrence include dietary hygiene and the presence of an associated metabolic disease. The metabolic blood and urine tests recommended by the Association Française d’Urologie (AFU) can be used to manage these last two problems.

As far as residual fragments are concerned, their presence leads to an early recurrence of stones because they form the bed for a new aggregation of crystals in the kidneys. Being able to reduce the rate of residual fragments in patients with the use of furosemide at the end of the intervention therefore seems essential in the management of recurrences in our patients. This will also improve our patients’ quality of life.

Indeed, lithiasis disease leads to chronic pain associated with acute pain that motivates consultations to the emergency for specialized management. This study is the first to evaluate the impact of forced diuresis with the use of furosemide on the stone-free rate after a fURS for destruction of kidney stone with laser.

**Trial registration:**

ClinicalTrials.gov Identifier: NCT05916963, first received: 22 June 2023.

EU Clinical Trials Register EudraCT Number: 2022-502890-40-00.

**Supplementary Information:**

The online version contains supplementary material available at 10.1186/s13063-024-08309-0.

## Background

### Background and rational

Lithiasis is a public health problem. It affects about 10% of the general population. This prevalence is increasing (multiplied by 3 in 40 years), partly due to changes in the population’s eating habits over the years [1]. The risk factors for the development of urinary stones are multiple: socio-economic status, environmental factors, genetic predisposition, and certain metabolic disorders [2]. The increase in metabolic syndrome plays a large role in the development of lithiasis disease in developed countries. The management of lithiasis is extensive. It ranges from active surveillance with or without expulsive treatment (alpha-blocker) to surgical removal of stones (flexible ureteroscopy [fURS] and percutaneous nephrolithotomy [PCNL]) and also includes extra-corporeal shock wave lithotripsy (SWL) [2]. The size, location, and density of the stone influence the choice of treatment [3, 4].

Over the past 20 years, fURS have dramatically changed the management of kidney stones and has become the most performed procedure for the removal and destruction of kidney stones. More than 40,000 fURS for stones are performed per year in France in common practice.

The lithiasis patient is a patient with a chronic disease requiring annual follow-up and who may suffer from multiple recurrences, with a recurrence rate at 5 years of 50% [1, 2].

Being able to reduce the rate of residual fragments in patients might reduce the risk of recurrence and therefore improve the quality of life. All this leads to the need to evaluate the interest of an adjuvant treatment associated with fURS (being the predominant treatment for kidney stones) to further decrease the stone-free rate in these lithiasis patients.

In the literature, we find as adjuvant treatments: post-urotherapy and forced diuresis.

The goal of post-urotherapy is to relocate stones trapped in the lower or middle calyces into the renal pelvis in order to increase their spontaneous clearance by the natural route. This can be done for small stones immediately or after SWL, fURS, or PCNL for residual fragments. The patient is placed in a special position (lateral safety position with Trendelenburg in the prone position at − 30°) allowing the orientation of the caliceal stem of the inferior and anterior calyx to be favorable to the evacuation of the stones. Mechanical percussion-vibration is then performed. A preliminary per os hydration is associated to increase the diuresis.

A retrospective, single-center study conducted by Lechevallier et al. in Marseille in 2015 [5] showed that it is a non-invasive, non-morbid, and well-tolerated technique. It is proposed for the complementary management of residual fragments after fURS or SWL or even asymptomatic stones of less than 5 mm.

Pace et al. [6] showed, in a paper published in 2001, that after SWL, the mechanical percussion and inversion group had a substantially higher stone-free rate than the observation group (40% versus 3%, respectively, *p* < 0.001).

It is therefore proven in these studies that post-urotherapy has a positive effect on the residual fragment rate after SWL or fURS for kidney stone destruction.

Forced diuresis with or without furosemide injection has been performed only in the context of SWL management. No study has ever associated forced diuresis with fURS.

In the article from Chiong et al. [7], published in 2004, evaluating the stone-free rate after furosemide injection post SWL, the radiologically documented complete stone clearance rate at 3 months for the control group was 35.4% and for the experimental group was 62.5% (*p* = 0.006).

A study published in 2015 by A. Ahmed’s team [8] showed a significantly (*p* = 0.030) higher stone-free rate in the furosemide injection group (78.3%) compared to the control group (61.1%) for stones located in the lower calyx after SWL. There were no significant differences between the furosemide injection group and control group in terms of adverse events which were all mild complications.

In the 2017 study by S. Sabharwal et al. [9], evaluating the impact of forced diuresis by injection of 40 mg of furosemide on the stone-free rate, better clearance was found in the experimental group (77.1%) compared to the control group (70.8%) after SWL, despite non-significant results (*p* = 0.49).

In the works of S Sohu et al. [10], published in 2019, after 2 months, the stone-free rate after SWL was much higher in the group with furosemide 40 mg injection and intravenous hyperhydration (77.0% vs 65.3% [*p* < 0.001]). Furthermore, for patients aged ≤ 40 years, the stone-free rate was significantly higher in experimental group than control group, at 89.2% vs 71.4% (*p* < 0.001). There was no significance difference in the complication rates between the furosemide group and the control one.

The study carried out by Kocaaslan et al. [11] investigated the efficacy of forced diuresis with 40 mg furosemide and IV hyperhydration prior to SWL for stones between 6 and 20 mm. No statistically significant difference was found between the groups; the stone-free rate was 69% in the control group and 71% in the treatment group (*p* = 0.758).

The team of Liying Dong et al. [12] carried out a review of the literature and a meta-analysis on the subject in 2020. Six randomized controlled trials containing 1344 patients were included in this meta-analysis, which compared diuretics with placebo on SWL treatment of urolithiasis. In the analysis, they are founding those diuretics on SWL treatment were more effective for the management of urinary stones. Compared with placebo, patients who received diuretics during SWL treatment had significantly higher successful stone clearance rate (odds ratio; 1.73, 95% confidence interval; 1.35 to 2.21, *p* < 0.001).

This systematic review and meta-analysis indicated that diuretics during SWL were effective in the management of urolithiasis with lower risk of complications.

There is no evidence in the literature for the efficacy of adjuvant treatment with forced diuresis after fURS.

The results of these various studies are summarized in Table 1.

**Table 1 Tab1:** Summary of the various studies

Study	Type of study	Year of publication	Type of treatment		Number of patients		Follow-up	Results
			Control group	Experimental group	Control group	Experimental group		
Chiong et al. [7]	Randomized, controlled	2005	SWL	SWL + IV HH	49	59	3 m	35.4% vs 62.5%, *p* = 0.006 Better elimination of stones with forced diuresis
Ahmed et al. [8]	Randomized, controlled	2015	SWL	SWL + furosemide (20 mg)	100	100	3 m	61.1% vs 78.3%, *p* = 0.03 Better elimination of stones with forced diuresis
Kocaaslan et al. [11]	Randomized, controlled	2015	SWL	SWL + furosemide (40 mg)	72	69	2 w	69% vs 71%, *p* = 0.758 Not significant
Sabharwal et al. [9]	Randomized, controlled	2017	SWL	SWL + furosemide (40 mg)	48	48	2 w	77.1% vs 70.8%, *p* = 0.49 Not significant
Sohu et al. [10]	Randomized, controlled	2019	SWL + IV HH	SWL + IV hyperhydration + furosemide (40 mg)	357	357	2 m	65.3% vs 77%, *p* < 0.001 Better elimination of stones with forced diuresis

*SWL* Extracorporeal shock wave lithotripsy, *HH* Hyperhydration, *IV* Intravenous, *PO* Per os, *w* Weeks; *m* Months

In view of the positive results of forced diuresis after SWL, we propose to carry out the first randomized, controlled, multicentric, superiority trial with a blinding evaluation analyzing forced diuresis with furosemide injection after fURS for laser destruction of kidney stones.

### Objectives

Primary objective of the study:To show that the injection of 40 mg of furosemide in slow intravenous (IV) during 10 min, after the procedure, increases the stone-free rate 3 months after a fURS for destruction of kidney stones with laser

Secondary objectives of the study:To show that the rate of early post-operative urinary tract infection (UTI) within the first post-operative month after fURS with laser destruction of kidney stones is lower in patients who received forced diuresis with injection of furosemideEvaluation of post-operative painSafety of the use of furosemide in patients treated by fURS for renal stone laser destructionEffect of the prescription of an alpha-blocker as usual treatment on stone-free rate, which will be assessed in a subgroup analysisEvaluation of agreement between the imaging analysis of the urologist and the specialized radiologist

### Trial design

FIRE Stones is a two-parallel group randomized, controlled, multicentric trial with a blinded assessment.

## Methods: participants, interventions, and outcomes

### Study setting

The study will be conducted in 9 French departments of urology, including 8 university hospitals and a private clinic.

### Eligibility criteria

#### Inclusion criteria

Males or females aged 18 to 80 years, with the need to perform a fURS with destruction of the kidney stones with laser for a stones of less than 3 cm, were included.

#### Exclusion criteria

Patient with contra-indication to furosemide, having furosemide as usual treatment, or requiring an injection of aminoglycoside or vancomycin before or during the procedure will be excluded. Participation in other interventional research with an investigational drug or medical device is also an exclusion criterion.

## Interventions

The experimental group will receive intravenous furosemide 40 mg, after the end of the surgical procedure, when the ureteroscope is removed from the renal cavities; the anesthetist or the anesthetist’s nurse will inject the experimental treatment. Furosemide 40 mg diluted in 50 mL NaCl 0.9% will be administered as a single slow (over 10 min) intravenous injection.

In the event of poor tolerance during the 10 min slow intravenous injection, this may be stopped at the discretion of the anesthetic team.

The bottles of furosemide are dedicated to the study and supplied by the sponsor. The furosemide prescription will be issued via a nominative prescription obtained from EnnovClinical (e-CRF) after randomization. The department will attach the two detachable labels from the ampoules used, send the original to the pharmacy, and keep a copy in the patient file.

After discussions between urologists, anesthetists, nephrologists and the pharmacovigilance department at Tours University Hospital, we decided to propose a dose of 40 mg of furosemide [12]. Furosemide is an old drug whose side effects are well known and controlled. Dosages of 20 or 40 mg are very low doses of furosemide. Some patients may take 500 mg of furosemide a day. Undesirable effects are therefore considerably lower for dosages of 20 and 40 mg. As part of a pragmatic study looking for a significant improvement in stone evacuation and the stone-free rate, we felt that the 40 mg dosage was preferable, as it could possibly demonstrate a difference that was not visible with 20 mg furosemide, without increasing the risk of complications associated with the drug. As this was the first study to assess the impact of forced diuresis on stone-free levels after fURS for laser destruction of kidney stones, we felt it was important to take every opportunity to find a significant difference, if any.

Treatment must not be administrated in rapid IV injection. Indeed, we chose to carry out a slow injection because the fast injection of furosemide can involve an ototoxicity being able to go until the temporary or final surdity. This risk increases with the dosage used.

The control group will receive standard of care corresponding to the performance of a fURS without injection of furosemide or other drugs.

## Outcomes

### Primary outcome

The stone-free rate at 3 months of the fURS for renal stone laser destruction will to be evaluated on the low dose abdomino-pelvic CT scan. A centralized review of the images will be performed by two specialized radiologists, in a blinded and crossed way to allow a homogenization of the results.

It was decided to carry out an abdominopelvic CT scan, which is more radiant than a renal ultrasound scan, as this examination is not operator-dependent and can therefore be reviewed by the referring urologist, as well as by several specialized radiologists, to ensure optimal analysis. It was therefore decided to use “low dose” abdominopelvic scans, guaranteeing minimal irradiation (irradiation comparable to a standard X-ray, i.e., 6 times less than a conventional scan), while maintaining optimal analysis of our endpoint [13].

We have designated as “stone-free” patients for whom no calculi were found on follow-up imaging but also if the residual fragments were less than 4 mm [9, 14], as described in the current literature.

### Secondary outcomes

The post-operative UTI will be assessed within 30 days after surgery on the combination of fever higher than 38.5 °C and/or chills and/or clinical symptoms (supra-pubic pain, dysuria, pollakiuria, urgency, urinary burning, back pain radiating to the genitals, hematuria) and/or positive urine culture with a significant bacteriuria threshold (depends on the germ isolated and the gender of the patient) [15].

The post-operative pain will be assessed on visual numerical (from 0 to 10) pain scale in the recovery room, in the service, and at the discharge. The use of opioids will be reported.

Furosemide adverse events will be assessed.

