The half-life of furosemide is 1 h to 1.5 h after injection. Considering that the product is completely eliminated from the body after 5 half-lives, a monitoring of 5 h to 7.5 h will be required to ensure optimal monitoring of patients after their injection, which corresponds to the postoperative monitoring in routine practice (in conventional or ambulatory units).

Evaluation of pain will also be assessed by nurses during hospitalization. Pain will be assessed using a numerical pain scale ranging from 0 to 10. This will be done at three time points: in the recovery room, in the service, and at the discharge.

The patient will be followed up for 3 months (± 2 weeks), after the surgery. Patients will use a follow-up book to carry out a self-assessment in particular on the UTI. As usually, patients should consult their general practitioner in the event of sign of infection. However, only the combination of some of these symptoms will be synonymous with a UTI, requiring the expertise of a general practitioner or urologist to distinguish between a real UTI and just the postoperative symptoms caused by the procedure performed in the excretory tract, corresponding to the healing of the urinary mucosa. The ECBU should only be carried out at the request of a doctor (general practitioner or urologist).

A phone call will be performed 1 month after the procedure. We will collect the potential event: fever > 38.5 °C, chills, clinicals symptoms, call or consultation with general practitioner or urologist within 30 days of surgery, ECBU performed within 30 days of surgery, antibiotics within 30 days of surgery. All adverse events presented by the patient since the intervention will be collected.

The patient will have to perform his/her low dose abdomino-pelvic CT scan without injection at 3 months after the operation (± 2 weeks).

We scheduled another phone call by the CRA at about 2 months post-operatively to remind the patient to have his non-injected low-dose abdominal-pelvic CT scan at 3 months (± 2 weeks).

The results of the CT scan should be brought back at the 3-month follow-up consultation with his/her referring urologist. The CT scan data will be interpreted by the urologist and retrieved for an anonymous reading by 2 radiologists in a blind process.

We will also collect the occurrence of UTI in the first post-operation month or other complications, using the patient’s memory and the participant diary noting information.

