## Sample size

The proportion of stone-free patients at 3 months is expected to be 95% in the furosemide group, as compared to 85% in the control group. Indeed, in the literature, the stone-free rate is estimated at 85% [16]. We hypothesize that our treatment will increase this percentage by 10% to have an impact in current. Considering a two-sided type I error level of 5% and a power of 90%, we need to randomize 374 patients.

Because patients will be pre-included, and randomized only at the end of the surgical procedure, we plan to include 416 patients, thus considering that 10 % of them will not be randomized.

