#### Statistical analysis of secondary outcomes

Proportion of patients with post-operative UTI within 30 days after surgery will be compared between randomization groups using the same approach as for the analysis of the primary outcome.

Visual numerical scale of pain in the recovery room, in the service, and at discharge will be analyzed using a mixed model. Proportion of patients who received opioids will be compared between randomization groups using the same approach as the one use for the analysis of the primary outcome.

Analysis of the occurrence of furosemide-related events will be descriptive.

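### The 30-day UTI outcome lets a single non-specific symptom count as an infection, which conflicts with the follow-up section's rule that a doctor-judged combination is needed

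*Protocol article*

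**What the plan says.** The first secondary objective (Objectives) is directional: to show a lower rate of early post-operative UTI with furosemide.

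The Secondary outcomes section says the infection will be "assessed within 30 days after surgery on the combination of fever higher than 38.5 °C and/or chills and/or clinical symptoms", and the list continues "and/or clinical symptoms (supra-pubic pain, dysuria, pollakiuria, urgency, urinary burning, back pain radiating to the genitals, hematuria) and/or positive urine culture" above a significance threshold. It gives no minimum number of items and requires neither a culture nor a diagnosis.

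The Participant timeline section (text after Table 2) states a different rule: "only the combination of some of these symptoms will be synonymous with a UTI, requiring the expertise of a general practitioner or urologist". The doctor is needed "to distinguish between a real UTI and just the postoperative symptoms caused by the procedure performed in the excretory tract". A post-operative urine culture (ECBU) is done only when a doctor asks for it. At the 1-month call, "We will collect the potential event: fever > 38.5 °C, chills, clinicals symptoms", together with contacts with a doctor, urine cultures and antibiotics within 30 days of surgery.

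The analysis is binary: "Proportion of patients with post-operative UTI within 30 days after surgery will be compared between randomization groups", by the logistic model used for the primary outcome.

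**The concern.** The two sections can classify the same patient differently. The outcome section can be scored so that one urinary symptom makes an event. The follow-up section rejects that, for a reason the protocol itself gives: healing of the urinary mucosa produces such symptoms without infection.

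Whoever derives the endpoint must choose between these rules, and the choice decides who is an event. If the literal wording is used, part of what is counted is ordinary recovery from ureteroscopy. Those false events occur in both arms and pull the comparison towards no difference. If the choice is left open until data are available, it may be made with the results in view. Urologists are not blinded, and the central blinded review covers the CT scans only.

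**Working it through.** **1. The two rules side by side**

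| Patient within 30 days | Secondary outcomes, literal and/or | Participant timeline |
|---|---|---|
| Haematuria only | can count | does not count |
| Urgency only | can count | does not count |
| Positive culture, no symptom | can count | not covered; the rule speaks of symptoms |
| Two symptoms, no doctor consulted | can count | no doctor's judgement, so not established |
| Fever, symptoms and positive culture, doctor diagnoses UTI | counts | counts |

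The rules agree only in the last row. Neither section names the combination required.

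**2. The plan's own figure**

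Inputs from Sample size and Implementation: 85% versus 95% stone-free, 1:1 allocation, and "Considering a two-sided type I error level of 5% and a power of 90%, we need to randomize 374 patients". The pooled-variance formula gives 188 per arm, 376 in total, against 374 stated. With 187 per arm the power is 0.900. Allowing for 10% not randomized, 374 / 0.90 = 415.6, so 416 as stated. The figure reproduces, and it concerns the primary outcome only.

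**3. Effect of literal scoring on the UTI comparison**

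The documents give no UTI rate and no symptom rate, so the rates below are assumptions. Let p be the true UTI rate and s the share of patients without UTI who have at least one listed item. Assume s is equal in both arms and every true UTI is captured.

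- Recorded rate = p + (1 − p)s
- Recorded difference = (p_control − p_furosemide)(1 − s)
- Power = Φ{[d − 1.96·√(2p̄(1 − p̄)/n)] / √[(p₁(1 − p₁) + p₂(1 − p₂))/n]}, where n = 187, p₁ and p₂ are the recorded rates, d is their difference and p̄ their mean (opposite tail ignored)

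Example with true rates 15% versus 5% and s = 0.30:
- Control: 0.15 + 0.85 × 0.30 = 0.405
- Furosemide: 0.05 + 0.95 × 0.30 = 0.335
- d = 0.070 and p̄ = 0.370
- Numerator: 0.070 − 1.96 × 0.0499 = −0.0279; denominator: 0.0498
- Power = Φ(−0.56) = 0.29

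| s | Recorded rates, true 15% vs 5% | Difference (points) | Odds ratio | Power | Power, true 10% vs 5% | Power, true 20% vs 10% |
|---|---|---|---|---|---|---|
| 0 | 15.0% vs 5.0% | 10 | 0.30 | 90% | 45% | 78% |
| 10% | 23.5% vs 14.5% | 9 | 0.55 | 60% | 21% | 54% |
| 30% | 40.5% vs 33.5% | 7 | 0.74 | 29% | 11% | 28% |
| 50% | 57.5% vs 52.5% | 5 | 0.82 | 16% | 7% | 16% |
| 70% | 74.5% vs 71.5% | 3 | 0.86 | 10% | 5% | 10% |

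The 15% versus 5% pair mirrors the primary-outcome rates (1 − 0.85 and 1 − 0.95), so its 90% starting power follows from that choice.

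**The case against.** The strongest reply is that the outcome sentence does speak of a combination, and the follow-up section uses the same word. The first could be read as listing components and the second as saying how to judge them. The article also condenses a fuller protocol, and the definition cites a source; either may hold the exact rule. This has force against one inference a reader might draw, that the outcome is plainly an any-of list. It is not: the wording is self-contradictory and permits any-of scoring. The reply does not remove the conflict, because a combination whose every link is and/or has no fixed meaning and neither section names the set required.

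A reader might also infer that false positives swamp the comparison. The documents give no rates to support that. With equal reporting, an assumed 10-point benefit becomes 9, 7, 5 or 3 points, which is attenuation and not disappearance. Nor does all the low power come from the wording: with a strict definition (s = 0), power is only 24.5% for 5% versus 2.5% and 45% for 10% versus 5%.

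Finally, a reader might infer that the diuretic could reverse the result by raising reports of frequency or urgency. That needs an invented difference in reporting between arms. The documents point the other way: one injection, a stated half-life of 1 to 1.5 h against a 30-day window, blinded patients, and randomization stratified by double J stent. Mostly non-differential misclassification is the reasonable expectation.

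**Conclusion.** The point holds as a conflict in a stated case definition. One section permits a single non-specific symptom, or a culture alone, to be scored as a UTI; another requires a doctor-judged combination and explains why isolated symptoms mislead. This goes beyond detail left to an analysis plan, because the protocol gives two incompatible rules for one binary endpoint.

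Under literal scoring the risk difference is multiplied by (1 − s), so any s above 0 pulls the effect towards the null. The size of the loss depends on s and on the true UTI rates, neither of which the documents give. It also rests on equal s in the two arms and full capture of true infections. The claim stops at dilution.

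The consequence is confined to a secondary outcome, and the primary outcome and the 374 and 416 figures stand. The rule should still be fixed before any outcome data are reviewed.

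**What to change.** Replace the two statements with one pre-specified derivation rule, cited in both sections and applied blind to allocation, under which an isolated symptom is not an event. One workable form:

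- **Event:** at least one of fever above 38.5 °C, chills or a listed symptom, together with either significant bacteriuria on urine culture or a doctor's diagnosis of UTI with antibiotics, within 30 days.
- **Sensitivity outcome:** culture-confirmed UTI only. A culture should not be compulsory for the main definition: it is done only on request, so uncultured infections would become non-events and the endpoint would depend on ordering practice.
- **Reported separately:** isolated symptoms, by arm.

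The 1-month call already covers fever, chills, symptoms, contacts with a doctor, cultures and antibiotics. The cost is wording and a derivation rule, plus a check that the form records the culture result and the doctor's diagnosis, and not only that a culture or consultation took place. Trial status reports no patients yet included, so at that date the rule could be set without sight of results.

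The downside is fewer counted events. The diagnosis arm of the rule also still depends on doctors, some of them unblinded urologists, which is why the culture-confirmed analysis belongs beside it.
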